## Abstract

**Background:**

Bariatric surgery may be indicated in patients with nonalcoholic fatty liver disease (NAFLD) to achieve and maintain the degree of weight loss required to ensure therapeutic effects. However, bariatric surgery is still underrecognized in the treatment of NAFLD, including its inflammatory subtype, nonalcoholic steatohepatitis (NASH). Moreover, there is a lack of follow-up outcome data on different types of bariatric surgery in patients with NAFLD. This study aims to adequately assess the effect of bariatric surgery on NAFLD remission in obese patients.

**Methods:**

This prospective multicentre observational follow-up study will include 142 obese patients with NAFLD scheduled to undergo one of the following surgical procedures: sleeve gastrostomy, Roux-en-Y gastric bypass, and one anastomosis gastric bypass. The primary outcome is the complete remission rate of NAFLD one year postoperatively, which is defined by liver fat fraction < 5% on magnetic resonance imaging; the secondary outcomes includes (i) changes in NASH and liver fibrosis biopsy findings, (ii) changes in body weight and abdominal adipose weight, (iii) resolution of obesity-related comorbidities, and (iv) incidence of adverse events. A long-term follow-up related to this study will also be conducted.

**Discussion:**

This study will provide a necessary and preliminary foundation for the early identification and targeted treatment of patients with NAFLD who can be referred for bariatric surgery, as indicated for management of obesity and metabolic disease.

*Trial registration:* Clinicaltrials.gov: NCT04366999. Registered 21 April 2020. (https://clinicaltrials.gov/ct2/show/NCT04366999).

## Background

Obesity and obesity-related metabolic diseases have become a global public health crisis. Non-alcoholic fatty liver disease (NAFLD) is one of the most common comorbidities in obese patients, with a prevalence of approximately 25% worldwide [1]. NAFLD is a major cause of end-stage liver diseases, ranging from non-alcoholic simple hepatic steatosis and non-alcoholic steatohepatitis (NASH) to fibrosis and hepatic cirrhosis [1, 2]. NASH is estimated to become the leading cause of liver transplantation in the next ten years, which will result in immense economic and health burden worldwide [3]. High-quality evidence has demonstrated that obesity is the main risk factor for NAFLD [1]. The overall prevalence of obesity among patients with NAFLD and NASH was reported to be 51.34 and 81.83%, respectively [1, 4]. Particularly, more than 90% of severely obese patients undergoing bariatric surgery have NAFLD [5]. Presently, the treatment for patients with NAFLD includes thiazolidinediones, vitamin E supplementation, etc. However, pharmacotherapy has limited clinical application. The best data currently available indicate that overall weight loss is the key to alleviate NAFLD progression [1, 6, 7]. Bariatric surgery may be indicated in obese patients with NAFLD to achieve and maintain the degree of weight loss required to ensure therapeutic effects. However, bariatric surgery is still underrecognized in the treatment of NAFLD, including NASH, its inflammatory subtype. Furthermore, due to the controversies associated with the existing reports, randomised control trials (RCTs) comparing different types of surgery for NAFLD and their outcomes are urgently needed [8–12]. Currently, obesity with NAFLD is not a definite indication for bariatric surgery worldwide, according to the current clinical guidelines. Therefore, an observational follow-up study is crucial to create and assess novel RCT designs.

“Bariatric surgery for non-alcoholic Fatty Liver Diseases in Individuals with Obesity (Base-NAFLD)” is a prospective multicentre observational follow-up study. This study aims to adequately assess the effect of bariatric surgery on NAFLD remission in obese patients: (i) to demonstrate the effectiveness of bariatric surgery for NAFLD, including NASH, (ii) to explore the differences in the effectiveness among three types of surgery—sleeve gastrostomy (SG), Roux-en-Y gastric bypass (RYGB), and one anastomosis gastric bypass (OAGB), and (iii) to develop a predictive model for surgical treatment using internal and external validation cohorts. This study will provide a necessary and preliminary foundation for the early identification and targeted treatment of patients with NAFLD, who need to be referred for bariatric surgery for the management of obesity and metabolic diseases.

## Methods

### Patient recruitment

The Base-NAFLD study is a prospective, multicentre, observational study. Patients scheduled to undergo one of the three types of bariatric surgery—SG, RYGB, and OAGB—at the participating centres, between 21 April and 31 December 2020, will be screened for consecutive enrolment in this study. The corresponding follow-ups will be conducted 2 years postoperatively until December 2022.

### Types of surgery

Surgical procedures include SG, RYGB, and OAGB. SG is the most common procedure, followed by RYGB. OAGB has been recognised by The International Federation for the Surgery of Obesity and Metabolic Disorders(IFSO)since 2018 [13, 14].

### Inclusion criteria

Patients meeting the following inclusion criteria are being considered for enrolment:Age between 16 and 65 years (all sexes).Diagnosed with obesity according to the World Health Organization criteria for obesity in Asian populations [15] and scheduled for a primary bariatric surgery at the participating centres.Diagnosed with hepatic steatosis preoperatively by radiologic (including ultrasonography, magnetic resonance imaging [MRI]-derived proton density fat fraction [PDFF]) or pathologic(intraoperative hepatic pathology) examinations.

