### Outcome measures

The primary outcome of this study is the complete remission rate of NAFLD one year postoperatively, as defined by liver fat fraction (LFF) < 5% on abdominal MRI.

Secondary outcomes are as follows:(i)changes in NASH and liver fibrosis biopsy findings, including the NAS (NAFLD activity score) [16] and SAF scores (steatosis [S], activity [A], and fibrosis [F])[17] one year postoperatively.(ii)changes in body weight and abdominal adipose weight, indicated by changes in the following parameters at each follow-up:percent excess weight loss (%EWL): %EWL = ([initial weight] – [postoperative weight])/([initial weight] – [ideal weight]) (ideal weight is defined as a body mass index [BMI] of 25 kg/m^2^ at each follow-up point)percentage of total weight loss (%TWL): %TWL = ([initial weight] – [postoperative weight])/([initial weight]) × 100(III)resolution of obesity-related comorbidities: blood glucose levels, lipid levels, and liver enzyme levels.(iv)incidence of adverse health events.

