### Data collection

A standard case report form was designed before the study and transferred to an electronic data capture (EDC) system (https://www.base-nafld.com). The EDC system provides a graphical user interface for data entry and has a validation component for data cross-checking and a reporting tool for descriptive analysis. Well-trained clinical research coordinators from Chuankang (Medicine Technology Co, Beijing, China) and Suzhou Plenitude (Bio-Medical Technology Co., Ltd., Jiangsu, China) will retrieve all required information from the medical records of included patients and upload them into the EDC system. Clinical research associates from Beijing Funhau Medicine Technology Co. are in charge of monitoring and providing feedback on the EDC system and for data quality control.

The case report form was designed to collect the following baseline and follow-up data (Table 1):Demographic data: study code, initial name, sex, date of birth, admission date, height, body weight, transumbilical abdominal circumference, smoking habits, and drinking habits.Disease history and medication usage: type 2 diabetes mellitus, hypertension, polycystic ovarian syndrome, and obstructive sleep apnoea hypopnoea syndrome; use of oral hypoglycaemic, insulin, anti-hypertensive medication, and lipid-lowering drugs.Preoperative examinations: routine blood tests and biochemical examinations, especially for ALT, AST, HbA1c, fasting blood glucose, fasting insulin levels, prothrombin activity time, and AFP; findings from abdominal ultrasonography and gastroscopy; and assessment of LFF levels from MRI.Surgical information: operation date, type of surgery, operation time, and surgical procedure information, including gastric pouch volume, Roux limb length, biliopancreatic limb length, stapler usage, and suturing.Liver pathology: findings from histopathological examinations of liver biopsy specimens obtained intraoperatively and one year postoperatively.Adverse events or serious adverse events.

**Table 1 Tab1:** Checklist of baseline and follow-up visits of patients enrolled in the Base-NAFLD study

	Visit 1 (Baseline)	Visit 2 (3-month intervals)	Visit 3 (6-month intervals)	Visit 4 (1-year intervals)	Visit 5 (2-year intervals)
Demographic data	●	●	●	●	●
Disease history and medication usage	●	●	●	●	●
Surgical information	●	✗	✗	✗	✗
Weight loss	✗	●	●	●	●
Routine blood tests	●	●	●	●	●
HbA1c	●	●	●	●	●
OGTT	●	✗	✗	○	✗
FBG	✗	●	○ ●	✗	●
Fasting insulin and fasting C-peptide	✗	○	○	●	○

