### Sample size determination

The Power Analysis and Sample Size software program (PASS, version 11.0 by NCSS, LLC) was used for sample size calculation, which was based on the estimated complete remission rate reported by previous retrospective studies [9–12] and the preliminary clinical results obtained from our centre. According to our preliminary data, 58 of the 69 patients (84%) who underwent bariatric surgery had preoperative underlying NAFLD, and the rate of complete remission was 55.2% three months postoperatively. To achieve a confidence interval width of 0.16 and an α value of 0.05 with a 78% complete remission rate, the estimated minimum sample size required for our study was 114. The withdrawal rate will be assumed to be 20% during follow-up; therefore, the sample size needed for this study will be at least 142 patients. Nevertheless, as this is an observational study, additional patients will be recruited for a subgroup analysis. According to the national registry in our country, the number of patients undergoing each type of surgery was found to be 82, 30, and 30 patients for the SG, RYGB, and OAGB groups, respectively.

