### Statistical analysis

SPSS 20.0 (SPSS, Inc., Chicago, IL, USA) and R software (R version 3.6.3; R Foundation for Statistical Computing, Vienna, Austria) will be used to perform statistical analyses. Continuous data will be presented as mean (standard deviation) or median (minimum, maximum) values, and categorical data will be presented as numbers (proportions/frequencies/percentages). P-values < 0.05 will be considered statistically significant.Comparison between preoperative and postoperative parameters: For paired continuous data, the paired t-test (normally distributed variables) or Wilcoxon’s signed-rank (skewed variables) will be used for analysis, whereas for paired categorical data, the chi-square test or Fisher’s exact test will be used for analysis.Primary outcomes: The complete remission rate of NAFLD in obese patients, along with the corresponding 95% confidence interval will be reported.Sensitivity analysis: A sensitivity analysis will be conducted to investigate the differences between the three types of surgery and BMI subgroups in terms of complete remission rate of NAFLD. Continuous variables will be tested by a paired t-test or Wilcoxon’s signed-rank test for paired samples, and the association between covariates and main outcomes will be tested using the chi-square test or Fisher’s exact test.Development and validation of the prediction model: Before building the model, the dataset will be divided into a training set—three-quarters of the enrolled patients will be randomly assigned to this set—and a validation set—the remainder of the patients will be assigned to this set. A multivariable logistic regression model will be used in which the response variable will be complete remission of NAFLD. The model will be built using stepwise selection based on the Akaike information criterion. The training model will be subsequently applied to the validation set. The model performance of both the training and validation sets will be evaluated using C statistics for discrimination, and the goodness-of-fit will be evaluated using Hosmer–Lemeshow test. A calibration curve will also be developed to examine the model fit. For both the training and validation sets, the predicted risk will be plotted against the observed risk for each of the 10 risk percentiles created from the dataset. Calibration will be evaluated using the Hosmer–Lemeshow goodness-of-fit test and chi-square test based on the predicted risk deciles. Results will be displayed as a nomogram to provide clinicians with an intuitive and quantitative tool to predict the probability of complete NAFLD remission in obese patients.

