## Discussion

Given the current understanding of the pathogenesis of NAFLD and its rising prevalence, an international expert consensus was reached, highlighting the need for a new definition for NAFLD as metabolic associated fatty liver disease (MAFLD) [19]. Obesity is one of the main criteria for MAFLD based on evidence indicating hepatic steatosis. Due to the lack of approved pharmacotherapies, bariatric surgery has the potential to ameliorate NAFLD in patients with obesity. According to the current literature, bariatric surgery significantly improves biochemical and histologic parameters in patients with NAFLD [8]. However, most studies on this matter are retrospective, single-centre studies that considered laboratory values as assessment measures, with limited ability to draw definitive conclusions [9, 10]. The primary outcome in our study is the complete remission rate of NAFLD at 1 year after bariatric surgery, as measured by MRI. Moreover, the changes in the liver biopsy findings pertaining to NAFLD activity and fibrosis staging scores will be calculated as important secondary outcomes.

NAFLD is diagnosed using several methods, including imaging, blood biomarkers/scores, or liver biopsy. Liver biopsy is deemed as the ‘golden standard’ method in patients without any history of alcohol or liver toxin exposure. As a surrogate for invasive measurement, laboratory values can assess NAFLD and liver fibrosis [20]. However, biochemical values, such as ALT and AST, cannot accurately and quantitatively evaluate hepatic steatosis, and the influence of liver injury on liver enzyme levels cannot be excluded [21]. Ultrasonography is a widely used first-line diagnostic modality but has limited sensitivity. It does not reliably detect steatosis of < 20%, and its performance is suboptimal in individuals with a BMI > 40 kg/m^2^ [19, 21]. Furthermore, computed tomography has limited ability in quantifying hepatic fat fraction [22]. MRI, as a non-invasive diagnostic modality, is an accepted reference imaging method and an alternative to liver biopsy for hepatic fat content assessment [22]. Moreover, PDFF calculated by MRI accurately estimates the presence of hepatic steatosis [23, 24]. Significant decreases in LFF features are visible on MRI after bariatric surgery [25].

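### Complete remission is defined only by one-year MRI liver fat below 5%, so a patient already below 5% before surgery who stays there counts as a remission

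*Protocol article*

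**What the plan says.** **Entry.** Under Inclusion criteria, the patient must be "Diagnosed with hepatic steatosis preoperatively by radiologic (including ultrasonography, magnetic resonance imaging [MRI]-derived proton density fat fraction [PDFF"), or steatosis may be shown by "pathologic(intraoperative hepatic pathology) examinations". Any one route is enough. No route carries an LFF cut-off.

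**Primary outcome.** Under Outcome measures it is the "complete remission rate of NAFLD one year postoperatively, as defined by liver fat fraction (LFF) < 5% on abdominal MRI". The Abstract gives the same definition. Neither place says what the LFF must have been before surgery.

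**Primary analysis.** Under Statistical analysis: "The complete remission rate of NAFLD in obese patients, along with the corresponding 95% confidence interval will be reported". The denominator is not limited by baseline LFF. The same remission variable is the response in the logistic prediction model and the outcome compared across procedures and BMI subgroups.

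**Baseline MRI.** Under Data collection the preoperative examinations include "assessment of LFF levels from MRI", and Table 1 marks abdominal MRI as mandatory at every visit, baseline included. The article does not use the baseline value for eligibility or for the primary denominator.

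**The concern.** The entry test and the outcome test are not on the same scale, and only the outcome has a threshold. A patient enrolled on ultrasound or on histology can have a baseline MRI LFF below 5%. If the value is still below 5% at one year, the patient meets the definition of complete remission although nothing has remitted on the scale used to judge it.

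The primary result is a single proportion without a control arm, so no comparison cancels such patients out. The confidence interval reflects sampling error only and does not cover this bias.

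The prediction model inherits the problem. Some of its events would be patients who met the endpoint before treatment, and any predictor related to low baseline liver fat would then partly predict remission by construction.

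**Working it through.** **1. The plan's own figure.** Sample size determination sets its target thus: "To achieve a confidence interval width of 0.16 and an α value of 0.05 with a 78% complete remission rate". The smallest n for which the exact (Clopper-Pearson) 95% interval at 0.78 has full width of at most 0.16 is 114, with width 0.1594. This matches the stated 114. Allowing for 20% withdrawal, 114 / 0.80 = 142.5, against the stated 142. The sample size is not in dispute. It supplies the yardstick: a planned half-width of about 0.16 / 2 = 0.08, or 8 points.

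**2. Bias formula.** Let q be the remission rate among patients with baseline LFF of at least 5%. Let f be the share of analysed patients who are below 5% at baseline and stay there. Then

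- reported rate = f + (1 − f)q
- bias = f + (1 − f)q − q = f(1 − q), which is never negative.

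**3. Numbers at q = 0.78.** The documents do not give f, so the values below are assumptions.

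| f | Reported rate | Bias, f × 0.22 | Rate among baseline LFF ≥ 5% if 78% were reported, (0.78 − f)/(1 − f) |
|---|---|---|---|
| 2% | 78.4% | +0.4 points | 77.6% |
| 5% | 79.1% | +1.1 points | 76.8% |
| 10% | 80.2% | +2.2 points | 75.6% |
| 20% | 82.4% | +4.4 points | 72.5% |

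The bias would equal the planned half-width only at f = 0.08 / 0.22, about 36%.

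**4. If some of these patients rise above 5%.** Now let f be the share below 5% at baseline, and s the proportion of them still below 5% at one year. The bias becomes f(s − q). It stays upward as long as s exceeds q, and it is largest at s = 1, the case in the table.

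**5. Precision after restricting the denominator.** At f = 10%, 114 × 0.90 = 102.6, about 103 patients, and the exact width at 78% rises from 0.159 to about 0.168. At f = 20%, 114 × 0.80 = 91.2 and the width is about 0.179. To keep 114 evaluable patients, enrolment must be 114 / [(1 − f) × 0.80]: 146, 150, 159 and 179 for f = 2%, 5%, 10% and 20%.

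**The case against.** The best defence is that remission presupposes disease, so the sponsor may never have meant to count a patient who started below 5%. The preliminary data point the same way: 58 of 69 patients had NAFLD before surgery, and the quoted 55.2% equals 32/58, a rate among patients with disease at baseline. The full protocol or analysis plan, not shown, may restrict the analysis set. This lowers the likelihood of harm but does not close the gap. The article does not say that NAFLD in those 58 was defined by MRI, and eligibility and the primary endpoint are stated here as rules which, followed literally, admit the wrong patients to the numerator.

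Three stronger readings are tempting and should be resisted.

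- **That ultrasound entry will bring in many patients below 5%.** The Discussion says of ultrasound: "It does not reliably detect steatosis of < 20%, and its performance is suboptimal in individuals with a BMI > 40 kg/m^2". The first half describes missed mild steatosis, not false positives. If anything, it suggests that ultrasound-positive patients are usually well above 5% and that f is small. The remark on high BMI gives no direction of error.
- **That the inflation is large because the true rate may be near 55%.** The 55.2% was observed at three months in preliminary data. Nothing supports using it as the one-year rate.
- **That baseline LFF is unknown.** It is collected, and the MRI is mandatory, so these patients can be identified at analysis and nothing is lost irrecoverably.

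Distortion of the comparison between procedures is likewise not shown. It would require f to differ between groups, and the documents are silent on that.

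**Conclusion.** The point holds as a defect in the endpoint definition, of unknown and plausibly small size. Every patient who begins and remains below 5% raises the primary rate and is a false event in the prediction model. At the planned 78%, the excess is 0.4 to 2.2 points for f between 2% and 10%, and 4.4 points at 20%, against a half-width of about 8 points. These figures rest on assumed values of f and on such patients staying below 5%. The study's main result is not shown to be in danger. The definition should nevertheless be corrected, because the error is systematic, the interval does not show it, and the data needed to remove it are already being collected.

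Separately, the inclusion criterion asks for a diagnosis before surgery yet accepts pathology obtained during it. The wording needs to be reconciled, but it has no shown effect on the estimate.

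**What to change.** - Define complete remission as MRI LFF of at least 5% at baseline and below 5% at one year.
- Take the primary rate and the prediction model over patients with baseline MRI LFF of at least 5%.
- Report the number with baseline LFF below 5%, and separately any without a usable baseline MRI.
- Give the rate over all enrolled patients as a sensitivity analysis.
- Restate the expected precision for the restricted denominator.
- Reconcile the requirement for a preoperative diagnosis with the acceptance of pathology taken at operation.

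**Cost.** No new measurement is needed. Precision falls slightly: at f = 10%, the exact interval width at 78% goes from 0.159 to about 0.168. Holding 114 evaluable patients instead would take about 159 enrolled, and the article already foresees recruiting beyond 142. The real trade-off is that patients with steatosis on histology but MRI LFF below 5% leave the primary set, although the Discussion treats biopsy as the reference method. They remain in the sensitivity analysis, and the report should say that the primary rate refers to MRI-defined steatosis.

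### Steatosis must be diagnosed before surgery, yet a specimen taken during surgery is accepted as sufficient: the timing wording contradicts itself and histology-only entrants are not set apart

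*Protocol article*

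**What the plan says.** All places are in the protocol article.

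- **Inclusion criteria**, timing: "Diagnosed with hepatic steatosis preoperatively by radiologic" means, with ultrasonography and MRI-PDFF named as examples.
- **Inclusion criteria**, same sentence, alternative route: "or pathologic(intraoperative hepatic pathology) examinations".
- **Data collection**, liver pathology item: "findings from histopathological examinations of liver biopsy specimens obtained intraoperatively and one year postoperatively". No preoperative biopsy is described.
- **Table 1**: abdominal MRI, abdominal ultrasonography and liver biopsy are all marked mandatory at Visit 1 (Baseline).
- **Patient recruitment**: "Patients scheduled to undergo one of the three types of bariatric surgery" at the participating centres "will be screened for consecutive enrolment in this study".
- **Abstract, Methods**: the cohort is described as "obese patients with NAFLD scheduled to undergo one of the following surgical procedures".
- **Background**, study aims: the results are to support "early identification and targeted treatment of patients with NAFLD, who need to be referred for bariatric surgery". The abstract's Discussion says much the same.
- **Outcome measures**: the primary outcome is the proportion with liver fat fraction below 5% on MRI one year after surgery.

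**The concern.** The eligibility sentence fixes a time for the diagnosis and then admits a route that cannot meet it. Two readings follow. If the time requirement governs, only imaging can qualify a patient and the pathology clause is empty. If the pathology clause governs, a patient without positive imaging is not yet eligible when the operation starts and becomes eligible when the specimen is read.

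Under the second reading two things are at stake:

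1. **Intended use.** The study is meant to help identify patients with NAFLD early and refer them. A patient whose steatosis is known only from an operative specimen was not identifiable for that purpose, yet would enter the nomogram's development data unmarked.
2. **Primary rate.** Remission is defined by a level at one year, not by a change. A histology-only entrant whose baseline MRI fat fraction is already below 5% is counted as a remission if the value simply stays where it was.

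**Working it through.** **Step 1: is the contradiction real?** Set the sentences side by side.

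| Element | Place | Content |
|---|---|---|
| Required time of diagnosis | Inclusion criteria | before surgery |
| Accepted routes | Inclusion criteria | imaging *or* intraoperative pathology |
| Times at which liver tissue is taken | Data collection | during surgery; one year after |

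The routes are joined by *or*, so pathology suffices alone. Nothing in the article limits it to confirming a positive image. Since no tissue is taken before surgery, no patient can satisfy both the time requirement and the pathology route by pathology alone.

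**Step 2: who is affected?** A patient with positive baseline imaging qualifies before surgery, whatever the biopsy shows. Table 1 makes MRI and ultrasonography mandatory at baseline. The affected group is therefore confined to patients who are (a) negative on imaging or (b) missing imaging, and who are positive on histology. The article gives no count or share for this group.

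**Step 3: the plan's own sample size.** From Sample size determination: expected rate 0.78, total interval width 0.16, α 0.05.

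- The exact (Clopper-Pearson) 95% interval at 0.78 has width 0.1601 for n = 113 and 0.1594 for n = 114. The smallest n meeting 0.16 is 114, as stated.
- Allowing for 20% withdrawal: 114 / 0.80 = 142.5, stated as 142.

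The present point leaves this calculation unchanged. It supplies only the yardstick for Step 4: a half-width of 0.16 / 2 = 8 points.

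**Step 4: how far could the primary rate move?** Let *s* be the share of the analysed cohort that enters by histology alone with baseline fat fraction below 5% and is still below 5% at one year. Assume everyone else remits at the planned 78%.

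Observed rate = *s* + (1 − *s*) × 0.78, so the rise = 0.22 × *s*.

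| Assumed *s* | Patients of 142 | Observed rate | Rise |
|---|---|---|---|
| 0% | 0 | 78.0% | 0.0 points |
| 5% | about 7 | 79.1% | 1.1 points |
| 10% | about 14 | 80.2% | 2.2 points |
| 20% | about 28 | 82.4% | 4.4 points |

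The values of *s* are assumptions, since the article gives none. Any effect is upward and, over this range, smaller than the planned half-width.

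**The case against.** The strongest defence is that this is loose drafting. Table 1 treats the biopsy as a baseline item, and a specimen taken at operation shows the liver before surgery has had any effect. On that view the time requirement means only that steatosis was present at baseline. The Discussion treats biopsy as the reference method and notes that ultrasonography is insensitive to mild steatosis, so there is good reason to keep histology as a route. It also says that PDFF estimates the presence of steatosis accurately, which suggests few histology-only patients. Moreover, everyone enrolled is already scheduled for surgery, and the nomogram predicts remission rather than the presence of NAFLD.

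Most of this stands. It argues against deleting the histology route and for a small affected group. It does not remove the contradiction in the wording, and it does not make histology-only entrants identifiable in the analysis.

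Three stronger readings are tempting but not supported:

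- **That enrolment is no longer consecutive.** Patient recruitment speaks of consecutive screening of scheduled patients. A series whose eligibility is settled at surgery can still be consecutive. Only the moment of eligibility is unsettled.
- **That about 9 to 23 of 142 patients are affected.** A reader might take the pilot's 58/69 = 84.1% with NAFLD and treat the other 11/69 = 15.9% as missed by imaging (0.159 × 142 = 22.6). Or one might set 84.1% against the 90% prevalence in the Background: (90 − 84.1)/90 = 6.6%, and 0.066 × 142 = 9.4. But the article does not say how the 58 were diagnosed, and the other 11 may have had no steatosis. The 90% refers to severely obese surgical patients and is given as a lower limit. The exact 95% interval for 58/69 is 73.3% to 91.8%, which includes 90%. The figures are compatible with zero.
- **That centres will apply opposite rules.** The wording permits this, but nothing shows it. Quality control provides for documented procedures, training and source-data verification.

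**Conclusion.** The point holds as a contradiction within the eligibility criterion, with a limited consequence. As written, a patient with negative or missing baseline imaging can qualify only after surgery has begun. That patient could not have been identified for referral and, with a baseline fat fraction already below 5%, can count as a remission without any change.

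The size is unknown and may be zero. The illustrated effect on the primary rate, 0 to 4.4 points for assumed shares of 0% to 20%, is an upper case for each share: it takes every histology-only entrant to be below 5% at both baseline and one year, and everyone else to remit at 78%. The planned sample size is unaffected. The case for acting is that the correction costs almost nothing and the route of entry may be hard to reconstruct later if it is not recorded.

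**What to change.** 1. Reconcile the timing in the Inclusion criteria with the accepted routes, for example by requiring steatosis to be diagnosed *at or before surgery*.
2. Record for each patient the route by which the criterion was met: MRI, ultrasonography, histology only, or a combination.
3. Report the primary remission rate with its 95% confidence interval for all enrolled patients and again without histology-only entrants.
4. Refit or re-check the nomogram without histology-only entrants, and say whether its performance changes.

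Resting eligibility on preoperative imaging alone would also remove the contradiction. It would, however, give up the method that the article itself treats as the reference, so it is a trade-off and not a necessary correction.

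The cost is a changed phrase, one database flag and one additional sensitivity analysis. No extra visit, test or patient is needed. If the group proves empty, items 3 and 4 reduce to a sentence saying so.
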